## Abstract

Soccer (football) is the most popular sport globally, with 265 million players across all ages and sexes. Repetitive subconcussive head impacts due to heading of the soccer ball can pose threats to healthy brain development and aging. Omega-3 fatty acids, especially docosahexaenoic acid (DHA) and eicosapentaenoic acid (EPA), may have neuroprotective effects, but it remains unclear what aspects of neural health benefit from DHA+EPA when faced with subconcussive head impacts. In a randomized placebo-controlled trial, 208 soccer players will complete baseline measures including demographics, blood sampling, dietary recalls, and psychological assessment. Participants will be randomly assigned to ingest DHA+EPA [3.4g/d: DHA 2.4g+EPA 1.0g] or placebo daily for 8 weeks followed by a subconcussion intervention phase. During the subconcussion intervention, participants will perform a session of 20 controlled soccer headings, with a second session 24 hours later. Blood samples, neuroimaging data, autonomic reactivity, and clinical measures (symptoms, oculomotor, cognition) will be collected pre-heading and 24-hour post-1^st^ session, 24-hour post-2^nd^ session, and 7-day post-2^nd^ session. The primary hypothesis is that DHA+EPA pretreatment will promote neuronal and astrocyte resiliency to subconcussive head impacts, as assessed by blood biomarkers of brain injury, axonal microstructure measured by diffusion tensor imaging, and whole-brain resting-state connectivity. It is proposed that pretreatment will preserve autonomic function, as assessed by the cold pressor test (CPT), as well as oculomotor and cognitive function, even after head impacts. Data from this trial will help clarify the combined effect of DHA+EPA on brain molecular, cellular, and physiological health in response to subconcussive head impacts. If the hypotheses are confirmed, the findings will support a highly practical intervention for mitigating the neurodegenerative cascade triggered by head impacts.

**Trial registration:** ClinicalTrials.gov NCT06736925

## Introduction

Subconcussive head impacts are incredibly common among soccer players due to heading of the soccer ball, and their potential long-term effects have been highlighted in recent studies [1,2]. Former professional soccer players were found to have a mortality rate from neurodegenerative disease [especially Alzheimer disease (AD)] 5 times that of controls and were 4 times as likely to receive dementia-related medications [1]. These risks were modulated by career length, and positions with high exposure to headings (defenders, midfielders) [3,4] were more affected [2]. Repetitive head impact can also induce acute changes in brain cellular and functional integrities, where soccer headings, American football tackles, and boxing have been shown to elevate circulating tau, NF-L, UCH-L1, GFAP, and S100B levels, indicative of neural/glial injury and inflammation [5–12], as well as impairments in neuro-ophthalmologic (e.g., convergence, saccades) [13–16] and vestibular functions [17]. Although policy/rule changes to minimize head impact exposure are a logical step, subconcussive head impact inherent to athletic drills are difficult to regulate (e.g., soccer heading, tackles in contact sports). It is vital to explore and rigorously characterize potential interventions to enhance brain resiliency to subconcussive head impacts.

### Prophylactic and therapeutic effect of omega-3 fatty acids (FAs) on neural damage

#### Preclinical evidence.

DHA and EPA and long chain omega-3 fatty acids (FAs); they comprise 97% of brain omega-3 FAs (mostly DHA), are enriched in neuronal plasma phospholipid membranes and promote neurite outgrowth [18]. Studies have suggested that DHA and EPA exert potent protective effects against experimental traumatic brain injury (TBI). For example, the importance of DHA in maintaining brain resiliency to TBI was noted by Desai et al.[19] such that after sustaining a controlled TBI, DHA depleted mice (70% loss of DHA in the brain due to dietary manipulation) exhibited slower recovery from motor deficits, greater anxiety-like behavior and cognitive deficits, and elevated levels of alpha spectrin II breakdown products (axonal injury markers) compared to DHA adequate mice [19]. Mills et al.[20] further demonstrated that compared to untreated rats, rats pretreated with DHA showed significant reductions in anatomical damage after TBI, as measured by β-amyloid precursor protein counts within injured axons, axonal bulbs, and enhancement of cell survival (↓caspase-3). The effects of DHA on these cellular responses translated into cognitive resiliency, where rats pretreated with DHA showed similar memory function after TBI compared to sham rats, whereas untreated rats showed significant cognitive declines after TBI [21,22].

#### Clinical evidence.

Clinical evidence supports the potential of DHA and EPA to mitigate neuronal injury and mental illness, reduce blood pressure [23–26], attenuate sympathetic hyperreactivity [27], and enhance autonomic-regulated gut microbiota [28]. Bailes et al.[29] reported a case series of 9 comatose patients with severe TBI who were supplemented with a high dose of combined DHA+EPA (16.2g/d). All patients’ GCS scores improved over time, and they showed a significant return of cognitive and physical functions. The studies by Heileson et al.[30] and Oliver et al.[31] supplemented college football players daily with 2g DHA+0.56g EPA or placebo and with 2g, 4g, or 6g of DHA or placebo, respectively, and examined serum NF-L (indicative of axonal injury) changes across a season. The DHA+EPA group maintained NF-L levels throughout the season, whereas the placebo group showed significant elevations in NF-L levels [30]. Especially the players who ingested 2g/d DHA benefited the most, by maintaining NF-L levels similar to baseline throughout the season, whereas the players on placebo showed 60%-120% increases in NF-L levels [31]. However, because the studies did not record number or magnitude of head impacts and failed to account for various extraneous variables (e.g., exercise, body damage), the mechanism underlying the effect of DHA+EPA against subconcussive head impact remain speculative. The proposed study will address this question using a heading model and multimodal assessments.

### Aims and hypothesis

The proposed study will define the role and effectiveness of DHA+EPA in enhancing neural health and resiliency to acute subconcussive head impacts.

### Specific aims

Aim 1: To test the hypothesis that DHA+EPA will promote neuronal and astrocyte resiliency to subconcussive head impacts, as assessed by a panel of blood biomarkers (NF-L, tau, GFAP, UCH-L1, S100B).Aim 2: To test the hypothesis that DHA+EPA will maintain axonal microstructure and functional connectivity after acute and cumulative soccer headings.Aim 3: To test the hypothesis that DHA+EPA will maintain normal sympathetic hyperreactivity after soccer headings, as reflected by a typical cardiovascular response to the CPT (cold-pressor test).Exploratory Aim 4: To explore the role of DHA+EPA in sustenance of neuro-ophthalmologic and cognitive functions following subconcussive head impacts.Exploratory Aim 5: To explore the interaction between attention-deficit/hyperactivity disorder (ADHD) and DHA+EPA, in response to subconcussive head impacts.

### Outcome measures

Our primary outcomes (Table 1) will be assessed by comparing group differences, specifically group (DHA+EPA vs placebo) x time interaction, at 24-hour post heading relative to pre-heading baseline. Secondary outcome measures (Table 1) will be assessed beyond 24 hours post heading, including 24 hours post 2nd heading session, and up to 7 days after 2^nd^ heading session.

**Table 1 pone.0321808.t001:** Outcome Measures.

Outcome Measure	Type	Test/Task and Description
Blood Biomarkers	Primary Outcome	The primary outcome analyses will be comparing group differences (group x time interactions) in blood biomarkers, specifically NF-L (neurofilament light), tau (picogram per milliliter), GFAP (glial fibrillary acidic protein; nanograms per milliliter), UCH-L1 (ubiquitin C-terminal hydrolase-L1; picograms per milliliter), and S100B (S100 calcium binding protein B; nanograms per milliliter).
Diffusion Tensor Imaging (DTI)	Primary Outcome	DTI will be used to derive mean diffusivity (MD; square millimeters per second) and fractional anisotropy (FA; a unitless value that ranges from 0 to 1, 0 = Isotropic, 1= Anisotropic) as indicators joint of axonal integrity (axonal microstructure) and connectivity of white matter tracts by measuring how water molecules move through brain tissues.
Sympathetic Reactivity	Primary Outcome	Sympathetic Reactivity will be measured by the Cold Pressor Test (CPT). CPT is a general assessment of the ability of the sympathetic nervous system to become activated. The main metric will be changes in mean arterial pressure (MAP) following soccer headings. This test will be performed by submerging a participant’s hand into cold water for 2 minutes while autonomic and hemodynamic variables are recorded. At each data collection, participants will be instrumented for the measurement of heart rate (electrocardiogram) and continuous blood pressure. Participants will rest quietly for ~10 minutes before the CPT begins. The test takes 2 minutes.
Oculo-Motor Function	Primary Outcome	Oculomotor function will be tested by Near point convergence (NPC) and the King-Devick test (KDT). NPC will be conducted Using the accommodative ruler, a target (14-point letter) will be moved toward the eyes at a rate of 1–2 cm/s. NPC will be recorded when participants report diplopia has occurred, or the tester observes eye misalignment. The assessment will be repeated twice, and the mean near point convergence value will be used for analyses. The King-Devick test (KDT) consists of a total of 145 saccades while rapidly reading numbers aloud to complete the test. The KDT will be administered on a tablet. The total time (in seconds) will be used for analysis.
Neurite orientation dispersion and density imaging (NODDI)	Secondary Outcome	NODDI metrics will be derived from the the diffusion tensor images using the NODDI toolbox v1.0 in Matlab. Maps of neurite density (ND), orientation dispersion (OD), and intracellular volume fraction (ICVF) will be generated.
Resting-state Functional Connectivity	Secondary Outcome	Resting-state connectivity will be examined throughout the whole brain and specific seeded regions including the dorsolateral prefrontal cortex (DLPFC), angular gyrus, and cingulate gyrus.
Cardiovagal Baroreflex Sensitivity (cBRS)	Secondary Outcome	Spontaneous cardiovagal baroreflex sensitivity (cBRS) will be collected over the last 5 minutes before the CPT. Baroreflex sequences of 4 consecutive cardiac cycles will be captured using WinCPRS software, for which directional changes in the R-R interval and corresponding systolic blood pressure will be identified. Sequences will be detected when changes in systolic blood pressure are ≥1mmHg and the variation in R-R interval is ≥5miliseconds. Only sequences with an R2 ≥0.85 will be deemed acceptable. The mean of the regression slope will be calculated as the cBRS gain and used for analysis
Heart Rate Variability (HRV)	Secondary Outcome	Leading up to and during the cold pressor test (CPT) heart rate will be monitored via 3-lead ECG. Resting-state heart rate variability and spontaneous cardiovagal baroreflex sensitivity (cBRS) will be monitored over the last 5 minutes before the CPT. Using the R-R interval data collected from the ECG recordings during 5 minutes of paced breathing, time domain analyses will be performed to estimate overall heart rate variability and provide insight into cardiac parasympathetic activity.
Cognition	Secondary Outcome	Cognitive function will be measured using the NIH Toolbox Cognition Battery, which has excellent reliability and validity to measure cognition in young adults and has construct validity among those with TBI. Multiple forms will minimize learning effects. This battery examines 5 cognitive domains (executive function, episodic memory, language, working memory, and processing speed) and takes 20 minutes to complete on a tablet.
Cerebral blood flow (CBF)	Secondary Outcome	Perfusion imaging will be acquired to examine cerebral blood flow.
Metabolomics	Secondary Outcome	Mitochondrial respiration related metabolites, including pyruvate, acetyl-CoA, citrate, isocitrate, alpha-ketogluterate, succinyl-CoA, succinate, fumarate, malate, and oxaloacetate will be assessed on blood samples. The aggregation of all metabolomic data will provide a comprehensive overview of the homeostasis of the participant following repetitive head injury.
Quantitative Susceptibility Mapping (QSM)	Secondary Outcome	Quantitative Susceptibility Mapping of whole brain, as well as regions of interest analysis, will be conducted to inspect the tissue and brain architectural response to head impacts and omega-3 fatty acid supplementation.
Genetic Markers	Exploratory Outcome	Several genetic markers that are known to associate with brain vulnerability will be assessed and regressed against our outcome measures. These genetic markers include, but not limited to, DARC, APOE, KIAA0319, BDNF, TPH2, COMT. Each marker will be compared to the other outcome measures to understand the full effect of the intervention on the genetic markers as a whole.
ADHD	Exploratory Outcome	Participants who meet criteria for ADHD diagnosis will be analyzed to address the interactive effects of DHA+EPA and head impacts in ADHD.

## Methods

### Subjects

This study will include 208 participants, who are between 18 and 30 years old and current or former soccer players with a minimum of five years of soccer heading experience. The recruitment has started since February 2025 until March 2028, and all data collection is expected to finish by July 2028. Primary analyses are anticipated to finish by June 2029.

Participants will be screened using the inclusion and exclusion criteria in Table 2. A participant may be withdrawn from the research without his/her consent if, they come to any session with intoxication, sustained head injury (e.g., concussion) during the study duration, exhibit any sign or action of violent behavior or verbal abuse toward research personnel. The Indiana University’s Institutional Review Board has approved the study protocol (#21334) on December 23, 2023.

**Table 2 pone.0321808.t002:** Inclusion and exclusion criteria.

Inclusion Criteria
18–30 years of age Current or former member of a collegiate, club, or professional soccer team Have 5+ years of soccer heading experience
**Exclusion Criteria**
Are currently pregnant Have had a head or neck injury within the past 6 months Have implanted metal/magnetic devices (e.g., orthodontic braces) Diagnosed with autonomic or cardiovascular disease (e.g., hypertension) Allergy to fish or shellfish Consuming omega-3 FA supplements including plant-based (e.g., flaxseed) in the past 3 months Consume oily fish (>2 servings/month: salmon, bluefin, swordfish, anchovies)

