### Protocol proposal

#### Trial design.

This randomized placebo-controlled trial will consist of 2 groups: (1) DHA+EPA and (2) Placebo (Fig 2). Written informed consent will be obtained from all participants by the study coordinators. If individuals meet inclusion/exclusion criteria, pre-supplement baseline data will be gathered, including demographics, blood spot sample for assessment of omega-3 FA composition, dietary recalls for estimation of antioxidant intake, and symptom checklist. Participants will ingest DHA+EPA or placebo supplements daily throughout the 8-week supplementation phase and the subconcussion intervention phase. Participants in both groups will be required to ingest the supplement while monitored virtually, via Zoom or Facetime. Female participants’ menstrual cycle (MC), as determined by self-report, which will be further validated by salivary progesterone levels, will be monitored during the supplementation phase to determine regular or irregular MC and MC phases. During the biweekly visit, a blood spot sample will be collected to measure DHA+EPA levels and other FAs in the blood. During the subconcussion intervention phase, participants will be fitted with a wrist-worn Actigraph to monitor their activity/sleep levels. The subconcussion intervention will involve performing 20 controlled soccer headings per session. Participants will undergo 2 sessions in a 2-day period. Blood sample, MR data, autonomic reactivity, and clinical measures (symptoms, oculomotor, cognition) will be collected at pre-heading and 24-hour post-1^st^ session, 24-hour post-2^nd^ session, and 7-day post-2^nd^ session. Fig 1 indicates the current status of enrollment and Fig 2 depicts the study flow.

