### Randomization and blinding

Using the *R* randomization function, randomly stratified IDs that correspond to study groups will be generated. Randomly stratified sequentially numbered IDs will be placed in sealed envelopes by a blinded statistician, and containers of identical appearance will be prepared by a study coordinator, who will oversee the allocation of correct supplementation. Participants will be blinded to their group assignment. For participants with a vegetarian diet, they will be nonrandomly assigned equally to each group.

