### Study interventions

#### DHA+EPA intervention.

Participants will receive a batch of supplements to last 2 weeks during bi-weekly visits and be instructed to ingest supplements during 1-min Zoom or FaceTime call with the research coordinator each day. For the DHA+EPA intervention, each soft gel capsule contains 480 mg of DHA, 205 mg of EPA, 145 mg of other omega-3 FAs, and 10 mg of vitamin E. Participants in the DHA+EPA group will ingest 5 capsules daily [a total of 3.4 g/d: DHA (2.4 g), EPA (1.0 g)]. Individual percentage changes in DHA+EPA composition at 8 weeks may be considered as a covariate in analyses if we observe heterogeneous changes in DHA+EPA levels. Organic soybean oil softgel capsules will be used as a placebo condition for the DHA+EPA capsules. One capsule contains 485 mg of organic soybean oil, including negligible amounts of DHA (1.1 mg), EPA (1.7 mg), and vitamin E (10 mg). Participants will ingest 5 capsules daily. The placebo capsule’s shelf life, composition, shape, and size are the same as the DHA+EPA capsules.

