### Sample size

Based on the sample calculation for each aim, we will recruit a minimum number of subjects needed to conduct all aims. Thus, 208 participants (n=104 per primary group) will be recruited. *Alpha level setting:* The primary groups (DHA+EPA vs. placebo) share 3 post-heading time points (1^st^ 24h, 2^nd^ 24h, 168h), which will be compared to the pre-heading baseline. Thus, we set the alpha level at 0.017 to account for multiple comparisons. Based on the estimated effect sizes and alpha level, a sample size of 90 (Aim 1), 74 (Aim 2), and 82 (Aim 3) per primary group will result in 90% power to detect the supplementation effect. We accounted for a dropout rate of 15%, resulting in n=104 per group needed to accomplish all aims.

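### The only listed allergy exclusion matches the DHA+EPA capsule and does not cover soybean oil, the placebo ingredient

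*Protocol article*

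**What the plan says.** The Subjects section makes Table 2 the screening instrument: "Participants will be screened using the inclusion and exclusion criteria in Table 2". Among the exclusion criteria in that table, the only one about allergy is "Allergy to fish or shellfish".

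The section on the DHA+EPA intervention describes both products. For the comparator it states "Organic soybean oil softgel capsules will be used as a placebo condition for the DHA+EPA capsules" and "One capsule contains 485 mg of organic soybean oil". The daily number is the same as in the active group: "Participants will ingest 5 capsules daily".

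The Trial design section sets the duration: "Participants will ingest DHA+EPA or placebo supplements daily throughout the 8-week supplementation phase and the subconcussion intervention phase". The Sample size section sets the split: "208 participants (n=104 per primary group) will be recruited". The Randomization and blinding section adds one exception to random allocation: "For participants with a vegetarian diet, they will be nonrandomly assigned equally to each group".

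No section mentions soy allergy, or allergy to any capsule ingredient other than through the fish and shellfish item.

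**The concern.** The plan treats allergy to an ingested product as a matter of eligibility, but its list fits only one of the two products. Fish or shellfish allergy relates to the DHA+EPA capsule. The corresponding question for the placebo capsule is not on the list, although the article gives that capsule's content in milligrams.

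What is at stake is the safety of an individual. The participants are soccer players volunteering for an experiment, and one who reacted to the placebo ingredient would have been exposed to a product chosen because it should do nothing. An eligibility question acts before exposure, whereas adverse-event monitoring acts after it. No estimate, error rate or sample size in the plan depends on the point.

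**Working it through.** **Inputs from the article**

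- Screening list: Table 2, by the Subjects section.
- Allergy item in Table 2: fish or shellfish only.
- Placebo: soybean oil, 485 mg per capsule, 5 capsules a day.
- Groups: 104 and 104, total 208.
- Intake: 8 weeks plus the heading phase. The two sessions are 24 hours apart, and the last visit is 7 days after the second.

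**Input not in the article (assumption)**

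- Share of entrants with soy allergy: 0.1% to 0.5%.

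**Step 1. Does the list admit a soy-allergic person?** Take someone aged 18 to 30 with the required soccer background, who meets no exclusion in Table 2 and reports soy allergy. All inclusion criteria are met and no exclusion applies, so this person is eligible as the list stands.

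**Step 2. Does another section close the gap?**

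- The medical history questionnaire appears under Baseline measures. It is not tied to an exclusion, and Trial design has baseline data gathered once eligibility is met.
- The reasons for withdrawal in the Subjects section are intoxication, head injury, and violent or abusive behaviour. None concerns allergy.
- The independent safety monitor deals with adverse events that have already occurred.

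None of these is an allergy screen.

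**Step 3. Share allocated to placebo.** The plan's own figures agree: 104 + 104 = 208, and 104 / 208 = 0.50. Vegetarians are not randomised but are divided equally, so the share stays at one half.

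**Step 4. Length and amount of intake.**

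- Days: 56 + 1 + 7 = 64, or 65 if the pre-heading visit falls on a separate day. This is 64 / 7 = 9.1 to 65 / 7 = 9.3 weeks. The article does not state this total. The sum assumes that heading starts directly after week 8 and that the phase ends at the 7-day visit.
- Daily amount: 5 × 485 mg = 2,425 mg of oil. This is an amount of oil, not of soy allergen. Without the protein content it does not measure risk.

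**Step 5. Number of people affected.**

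| Assumed share with soy allergy | Expected among 208 | Expected on placebo (half) |
|---|---|---|
| 0.1% | 0.001 × 208 = 0.21 | 0.10 |
| 0.5% | 0.005 × 208 = 1.04 | 0.52 |

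For scale, the planned 15% dropout is 0.15 × 104 = 15.6 participants per group.

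**The case against.** The strongest reply is that this is a journal article condensing a protocol approved by an ethics board. The full protocol, the screening form and the consent form are not shown, and a question about ingredient allergy may well be in one of them. That stands as a limit: the article does not prove that soy allergy goes unasked in practice. It does not remove the point, because the article presents Table 2 as the list used for screening, and that list includes the allergy relevant to one product and omits the one relevant to the other.

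A second reply is that exposure to soybean oil is not the same as exposure to soy allergen. This also stands. The article gives neither the refinement nor the residual protein, so the size of the risk is unknown and may be low.

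Three stronger readings are tempting, and the article supports none of them.

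- *A site would have to enrol a soy-allergic person.* Nothing says so. Criteria limit who may enter; staff may use judgement, and the person may decline at consent.
- *Blinding prevents such a person from being kept off placebo.* The article says only that participants are blinded, and a coordinator prepares the containers and oversees allocation. It is randomisation that should prevent steering.
- *Reactions on placebo would distort retention or the safety comparison.* At most about half a person is expected on placebo, against roughly 16 planned dropouts per group. Neither Table 1 nor the Data analysis section lists a between-group safety comparison.

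**Conclusion.** The point holds as a mismatch between two stated items: the allergy exclusion in Table 2 and the composition of the placebo capsule. A person reporting soy allergy passes every listed criterion and, if randomised, has a one-in-two chance of daily soybean oil for about 64 to 65 days.

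It is a small point. On the assumed share of 0.1% to 0.5%, it concerns 0.2 to 1 entrant in the whole trial, and half as many on placebo. The individual risk cannot be quantified from the article, and no trial result would change. It is worth acting on because the remedy is very cheap and the risk, whatever its size, can be avoided. The conclusion rests on Table 2 being the complete list used at screening, as the Subjects section presents it.

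**What to change.** The sponsor should reconcile Table 2 with the description of the two capsules in one of two ways. Either the allergy criterion, asked of everyone before randomisation, covers the ingredients of both capsules, or the protocol states why the placebo ingredient needs no exclusion, for example on the basis of the oil's refinement if that can be documented. Which of these is appropriate is for the sponsor and its clinical advisers. If the full protocol or the screening form already covers the placebo ingredient, it is enough to bring Table 2 into line with it.

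The cost is one line in Table 2, one screening question and a negligible loss of eligible participants; the sample size is unaffected. The timing is favourable: the article gives recruitment as running to March 2028 and reports that nobody had reached outcome data collection as of March 2025. The change would therefore cover those still to be screened, and the same question can be put to participants already enrolled.
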